## Abstract

**Background:**

Dissemination of clinical practice guidelines alone is insufficient to create meaningful change in clinical practice. Quality improvement collaborative models have potential to address the evidence-practice gap in dementia care because they capitalise on known knowledge translation enablers and incorporate optimal approaches to implementation. Non-pharmacological interventions focused on promoting independence are effective and favoured by people with dementia and their carers but are not routinely implemented. The objective of this translational project is to assess the impact of quality improvement collaboratives (QICs) on adherence to non-pharmacological recommendations from the Clinical Practice Guidelines for Dementia in Australia.

**Methods:**

This project will employ an interrupted time-series design with process evaluation to assess the impact, uptake, feasibility, accessibility, cost, and sustainability of the QICs over 18 months. Thirty clinicians from across Australia will be invited to join the QICs to build their capacity in leading innovation in dementia care. Clinicians will participate in a training program and be supported to develop and implement a quality improvement project unique to their service context using plan-do-study-act cycles. Regular online meetings with their peers in the QIC will facilitate benchmarking and problem-solving. Clinicians will describe their practice via monthly checklists, and guideline adherence will be determined against a set of defined criteria. Phone interviews with up to 180 client dyads will be used to assess satisfaction with care and client outcomes. Clinician interviews and field note data will be used to explore implementation and costs. Involvement of people with dementia and carers will be embedded in the study design, conduct, and reporting, in addition to clinical and industry expertise.

**Discussion:**

The quality of dementia care in Australia is largely dependent on the clinician involved and the extent to which they apply best available evidence in their practice. This study will determine the elements of this multifaceted implementation strategy that contributed to guideline adherence and client outcomes. The findings will inform future translational approaches to improving care and outcomes for people with dementia and their carers.

**Trial registration:**

Registered with the Australian New Zealand Clinical Trials Registry 21 February 2018 (ACTRN12618000268246).

## Background

Care for people with dementia and their carers is complex because of the condition’s multi-domain symptom profile, progressive and individualised course, and wide-reaching impact on the individual, their family, and the broader community [1]. In Australia and elsewhere, the quality of care received depends largely on the health professional involved and the extent to which they apply best available evidence in their practice [1–3].

The 2016 release of the *Clinical Practice Guidelines and Principles of Care for People with Dementia in Australia* (the Guidelines) included a systematic overview of evidence-based and best practice care that should be provided to people with dementia and informal carers (hereafter referred to as ‘carers’) in Australia [2]. However, dissemination of guidelines via promotion or word-of-mouth is insufficient to effect change in clinical practice [4]. Historically, implementation of clinical practice guidelines has occurred via two mechanisms: first, ‘early adopters’ attempt to implement recommendations in practice but do so in an unpredictable manner because they rarely have theoretical or methodological skills in implementation [5, 6]. Second, research teams conduct more rigorously designed implementation projects such as stepped wedge or cluster randomised trials in partnership with health or aged care services. Typically, these projects involve identification of barriers followed by the use of tailored interventions strategies which may include training, education, reminders, and audit and feedback [7]. Such projects usually focus on changing a single health professional behaviour and often result in only modest effects [8]. Additionally, sustainability of the change can be jeopardised when research resources are withdrawn [6].

More effective methods of guideline implementation are required based on the knowledge that health care professional behaviour is influenced by a wide range of personal and contextual factors. One systematic review identified 57 clusters of factors that played a role in professional practice [9]. In dementia care, barriers to knowledge translation include insufficient time to implement strategies; a lack of financial, leadership, or staff support; inadequate levels of knowledge or training; high staff turnover; inappropriate staffing or resources; lack of perceived ‘power’ in creating change; and previous unsuccessful attempts to implement change [3, 10]. Effective implementation of evidence in this context requires integrated, multimodal learning strategies that are tailored to the learner preferences, allow learners to ‘try-out’ new knowledge with expert follow-up, use simple messaging, provide incentives, and target the whole workplace rather than the individual health professional [3].

A quality improvement collaborative (QIC) is an innovative knowledge translation strategy incorporating these principles. Collaboratives bring together health professionals from multiple sites to facilitate learning about and sharing of methods to improve care. They generally include five elements: (1) focus on a specific healthcare topic, (2) participants from multiple sites, (3) a group of clinical and quality improvement experts available to guide the QIC members, (4) a set of structured activities to promote collaborative learning, and (5) a model for improvement that tracks progress against measurable aims [11, 12]. The QIC model is based on evidence that assessing one’s own progress and benchmarking with other professionals can facilitate faster and wider implementation of quality improvement practices [13]. QIC models have potential to address the evidence-practice gap in dementia care because they capitalise on known knowledge translation enablers: sufficient knowledge, access to feedback, a combined learning experience, formulating an incremental action plan, iterative practical experience with new knowledge, and realistic goal setting.

Quality improvement collaboratives have been successfully implemented to increase rates of breast feeding [14] and organ donation [15], reduce central line-associated bloodstream infection [16], and decrease post-stroke length of stay [17]. To our knowledge, QICs have not yet been used as an implementation strategy in community-based dementia care. Whether they are an accessible, feasible, cost-effective, and sustainable method of improving guideline adherence in dementia care is not known.

### Objectives

The primary aim of this project is to implement and sustain improvements in post-diagnosis care for people with dementia and their carers by increasing adherence to three key recommendations from the *Clinical Practice Guidelines for Dementia in Australia* [2]:People with dementia living in the community should be offered occupational therapy (reflecting evidence-based programs)People with dementia should be strongly encouraged to exerciseCarers and family of people with dementia should have access to programs that provide respite and support to optimise their ability to provide care for the person with dementia.

This will be achieved by establishing three nationwide QICs (of approximately ten health professionals and their sites each) who regularly work with people with dementia and their carers. The three guideline recommendations were chosen to be implemented because adherence to them is known to be poor. Occupational therapy intervention involving home modification, education, problem solving, and activity engagement is shown to be cost-effective [18], yet in practice occupational therapists focus on assessment at the expense of intervention [19]. People with dementia are not routinely encouraged to exercise or participate in physical activity [20] despite exercise being the most effective intervention demonstrated to delay functional decline [21]. Supporting carers of people with dementia to maintain their wellbeing and to independently problem solve and manage their own needs can reduce negative carer impacts as well as delaying functional decline and reducing the occurrence of changed behaviours in the person they care for [22, 23]. Yet these types of programs are not widely available, and carers report that they need more education, skills counselling, respite, and emotional support to help them in their caring role [24, 25]. Implementation of these guideline recommendations reflects the priorities of people with dementia and carers, who have called for improved post-diagnostic care which facilitates independence and social engagement for people with dementia and provides effective support for their carers [26]. The recommendations are low-cost, acceptable, and feasible interventions that reflect broader policies around healthy ageing [27].

The secondary aim of this project is to assess the impact of the QIC on experiences and outcomes for people with dementia and their carers.

The research questions are:Can the establishment of a national dementia QIC increase adherence to three non-pharmacological recommendations from the guidelines? If so, are increases sustained?How feasible is the establishment of the QICs?What is the impact of the QIC on experiences and outcomes for people with dementia and carers?What is the return on investment (cost-benefit) of establishing QICs?How does participation in the QIC build knowledge and skills in quality improvement among the implementation clinicians?How acceptable is the addition of quality improvement implementation skills and knowledge to clinicians’ existing skill sets, workload, and responsibilities?What is the impact of involvement of people with dementia and carers in project design, conduct, and reporting?

## Methods

### Design

An overview of the project per guidelines by Proctor et al. [28] appears in Table 1. The impact of QICs on guideline implementation and outcomes for people with dementia and carers (‘client dyads’) will be evaluated in this implementation research project using an interrupted time-series design [29]. Interrupted time series is a strong evaluative design for estimating the impact of an intervention in non-randomised settings because it allows for detailed assessment of longitudinal trends associated with an intervention [30]. Feasibility, acceptability, cost-effectiveness, and sustainability of the model will be evaluated using an inbuilt mixed-methods process evaluation [31]. Both administrative data and data collected from participating health professionals, their employing organisations, and their clients with dementia and carers will inform the outcomes for this study.

**Table 1 Tab1:** Overview of project per guidelines by Proctor et al. [28]

Action	Description
Name it	Establishment of QICs to improve care for people with dementia and their carers
Define it	QICs enable rapid, sustainable improvements in care by bringing together health services to learn together, share ideas, and benchmark outcomes
Specify it	
a) The actor	The project team establishes and supports the QICs; Implementation clinicians form the QICs and conduct quality improvement (using PDSA cycles)
b) The action	Completion of an online training course, development of a site-specific implementation plan, and enactment of this plan (using PDSA cycles)
c) Action target	“Implementation clinicians”: health professionals across Australia who have some leadership responsibilities yet are still closely connected to the delivery of services and can introduce changes to practice
d) Temporality	The clinicians will participate in online training, develop a sites-specific implementation plan, and then enact the plan.
e) Dose	Seven education modules of 2 hours each, to be completed over 8 weeks; 11 virtual QIC meetings
f) Implementation outcome affected	Primary outcome: adherence to recommendation as described in the criteria in Table 3.
g) Justification	The intervention was designed to match with factors known to enable evidence-based care for people with dementia and their carers and to be relatively ‘light touch’ and promote rapid change

*Abbreviations*: *PDSA* plan-study-do-act, *QIC* quality improvement collaborative

Participating clinicians will be taught and supported to undertake a quality improvement project using a framework modelled on the Institute for Healthcare Improvement Model for Improvement [32]. They will learn about key change management models, conduct stakeholder analysis, and assess their organisation’s readiness for change. They will use plan-do-study-act (PDSA) methods to make iterative and self-directed quality improvements. Iterative quality improvement methods allow for clinicians to learn by testing practice changes, rapidly assess their impact, and adapting according to feedback and reflection [33, 34].

### Context and setting

Formal support services for people with dementia in Australia are primarily delivered via hospitals and the Commonwealth subsidised aged care system [35]. Diagnosis occurs in primary care, specialist physician rooms, or hospital outpatient settings, but psychoeducation and service navigation and provision after this time vary. Therapy services to optimise function and independence are available in some, but not all, settings. People with dementia and their carers can access helplines and advisory services, and subsidised ongoing home care packages are available (based on need) with the primary aim of maintaining independence and delaying institutionalisation. Programs that provide respite for carers are available as well as short- or long-term care accommodation options, and these may include some access to regular physiotherapy, occupational therapy, and other allied health services. Younger people with dementia (under the age of 65) are eligible for disability support packages and can choose to move to the aged care system when they turn 65 or remain in the disability sector. Overall, service provision is fragmented and varies according to demographic, organisational, and policy factors [36–39]. We aim to recruit from a broad range of geographical and professional settings to gather a variety of perspectives about the acceptability and effectiveness of the QIC methodology.

### Participants

Participants in this project include the health professionals (*implementation clinicians*), their workplaces (*implementation sites*), and the people with dementia and/or carers to whom they provide service (*client dyads*).

Implementation clinicians will be health professionals across Australia who regularly work with people with dementia and/or their carers, have influence within their workplace (and possibly leadership responsibilities), and maintain a clinical workload. Implementation clinicians are sought from a variety of service contexts, professional backgrounds, and geographical locations. Recruitment will occur via targeted advertising with professional associations, aged care organisations, peak bodies, and health services. Clinicians who apply to join the QIC will be assessed for suitability based on their experience, seniority within their organisation, and existing caseload of people with dementia and/or carers. They will be required to demonstrate that they have the support of their management to participate. Eligible implementation clinicians will:Be medical, allied health, or nursing professionals registered with a professional bodyRegularly treat/work with people with dementia and/or their carers (i.e. at least twice a week)Have some influence within their workplace (e.g. via leadership responsibilities)Maintain a clinical workload of at least 30% of their working hoursGive informed written consentHave signed approval to participate from their manager/supervisor

Implementation clinician workplaces will participate in the collaborative as ‘implementation sites’. An implementation site may include a general practice, a community care organisation, a day therapy centre, a memory clinic, a residential care facility, a hospital department, or any other organisation providing care for people with dementia. Direct managers/supervisors of implementation clinicians will participate in the process evaluation to gather their perspectives on the QIC and change management.

Client dyads will be existing patients with dementia and/or their carers within the caseload of the implementation clinician at the implementation site. Strict inclusion criteria will not be applied, and implementation clinicians will be asked to use their judgement; eligible people with dementia will be any client with a diagnosis of dementia (or suspected dementia) who attends a consultation with or without a carer. Carers will be any person attending the consultation who provides substantive care for a person with dementia and identifies as a carer. Implementation clinicians will complete the checklists about their consultation with each person with dementia (or carer, or dyad, where applicable) they see and return these to the study team. They will also ask for verbal assent (from both members of the dyad, where applicable) to pass contact details onto the study team for the purposes of two follow-up phone interviews. The study team will randomly select one dyad (per clinician) from among those assenting each month to receive these phone interviews (details below), for a total of 180 dyads.

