### Analysis

#### Quantitative analysis

Guideline adherence and client outcomes over time will be evaluated with a segmented regression analysis using the PROC NLIN function of SAS version 13.2 [63]. This technique uses modelling to draw conclusions about an outcome (in this case guideline adherence) across distinct segments of time (in this case, before and after quality improvement implementation) [64]. Data points for the time series will be the extent of guideline adherence each month over 18 months. Potential confounding variables will be fitted as covariates, and the most parsimonious model will be determined via stepwise backward elimination. The hypothesised outcomes of interest for this study are level and trend changes reflecting increasing adherence to the relevant guideline recommendation after the intervention (post-education quality improvement implementation) and over the 18 months. We will also calculate the counterfactual value and its proportionate distance from the actual estimated value [65]. The PROC AUTOREG function will be used to control for autocorrelation [63].

The sample size calculation for segmented regression analysis is related to the estimated number of time points at which data will be recorded. It is necessary to have enough time points before and after the intervention. This study incorporates 18 months of data collection (9 months pre-intervention and 9 months post-intervention) and is powered at 83% to detect a minimum 15% change in guideline adherence based on an estimated effect size of 1, autocorrelation of 0.3, and *α* = 0.05 [66]. This change in guideline adherence was used for power analysis based on literature suggesting an average of 10–15% improvement in adherence from traditional guideline dissemination activities [7]. Per recommendations from Wagner et al. [65], clinicians will submit up to ten checklists for each data point in the time series (for a total of up to 300 checklists each month) to achieve an acceptable level of variability of the estimate at each time point. The study design therefore meets the criteria for a robust interrupted time-series [67].

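### The monthly selection rule (up to 540 dyads) and the stated total of 180 disagree by up to a factor of three, and nothing fixes how the 180 are split before and after the intervention

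*Protocol article*

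**What the plan says.** All references are to the protocol article.

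- **Participants** gives a rate and a total in one sentence: "select one dyad (per clinician) from among those assenting each month to receive these phone interviews (details below), for a total of 180 dyads".
- **Abstract, Methods** gives the number of clinicians, "Thirty clinicians from across Australia will be invited to join the QICs", and presents the total as a maximum: "Phone interviews with up to 180 client dyads will be used to assess satisfaction with care and client outcomes". **Objectives** agrees on the number of clinicians, with "three nationwide QICs (of approximately ten health professionals and their sites each").
- **Quantitative analysis** gives the duration, "This study incorporates 18 months of data collection (9 months pre-intervention and 9 months post-intervention"), and the method: "Guideline adherence and client outcomes over time will be evaluated with a segmented regression analysis".
- **Guideline adherence** (under Outcomes) again describes monthly interviews with randomly selected dyads, up to 5 weeks after the consultation. It uses them to verify the clinicians' checklists. People with dementia who attend alone are not telephoned.
- **Service and client-level outcomes** adds a second interview up to 7 weeks after the first. Satisfaction is asked in all three collaboratives, quality of life in two (exercise and occupational therapy), and carer burden in one (carer support).

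**The concern.** A sampling rate, a number of clinicians and a duration together determine a total. Here the implied total is three times the printed one, so whoever runs the interviews has to decide which instruction to follow.

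That decision affects what the data can show. The secondary aim concerns the impact of the collaboratives on experiences and outcomes of people with dementia and carers, and that needs client data from both sides of the intervention. The same interviews are the named check on checklists that clinicians complete about their own practice, and the Discussion relies on them against responding bias. If monthly selection is applied until 180 dyads have been reached, the sample leans towards the early months, which are pre-intervention. How far it leans depends on how often a clinician-month produces an interviewed dyad, and the article gives no figure for that.

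**Working it through.** **Inputs.** Clinicians: 30 (Abstract; three collaboratives of about ten in Objectives). Months: 18, as 9 + 9 (Quantitative analysis). Rate: 1 dyad per clinician per month (Participants). Stated total: 180 (Participants; a maximum in the Abstract).

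**Step 1. Try to reproduce 180.**

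30 clinicians x 18 months x 1 = 540, and 540 / 180 = 3.

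Other products of figures in the article:

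| Product | Result | Comment |
|---|---|---|
| 30 x 9 | 270 | one period only; not 180 |
| 30 x 11 (number of virtual meetings) | 330 | not 180 |
| 30 x 6 | 180 | needs a 6-month interview window, which is not stated |
| 10 x 18 | 180 | is one collaborative, but 180 is given for the whole project |

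So 180 follows only with an extra condition that the article does not give.

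**Step 2. Allow for incomplete yield.** Let y be the proportion of clinician-months that produce an interviewed dyad. The article gives no value for y, so a range is shown.

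- Total over 18 months without a cap = 540y. For this to equal 180, y = 180 / 540 = 1/3.
- Month at which 180 is reached = 180 / (30y) = 6/y.
- Dyads selected in the 9 pre-intervention months = the smaller of 270y and 180.

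If 180 is a cap filled in order of time:

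| y | Month 180 is reached | Pre-intervention | Post-intervention |
|---|---|---|---|
| 100% | 6.0 | 180 | 0 |
| 80% | 7.5 | 180 | 0 |
| 66.7% | 9.0 | 180 | 0 |
| 60% | 10.0 | 162 | 18 |
| 50% | 12.0 | 135 | 45 |
| 40% | 15.0 | 108 | 72 |
| 33.3% | 18.0 | 90 | 90 |

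At full yield even the last second interview falls before the intervention: 5 + 7 = 12 weeks = 84 days, 84 / 30.44 = 2.8 months, and 6 + 2.8 = 8.8 months.

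**Step 3. An even spread of 180.** 180 / 18 = 10 dyads a month. All 10 contribute to satisfaction, about two thirds (6.7) to quality of life and about one third (3.3) to carer burden. Each period then has 90 dyads: 90 for satisfaction, 60 for quality of life and 30 for carer burden.

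**The case against.** **540 is a ceiling.** Selection is only from dyads that assent, people attending alone are not called, residential facilities are eligible sites, and clinicians may withdraw. The Abstract's wording makes 180 a maximum. All of this stands, and it is why the discrepancy is put at up to a factor of three. It does not reconcile the figures: 180 would need a yield of one third, which is not stated, and each clinician reports up to ten consultations a month and needs only one assenting, callable dyad. A cap also still needs an allocation over time.

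**A reader might infer that the plan leaves no post-intervention client data.** The article does not support that. It needs 180 to work as a stopping quota filled in sequence and a yield of at least two thirds, and the article states neither. Monthly interviews and a segmented regression of client outcomes both indicate that interviewing was meant to cover both periods. The loss is a risk that the text leaves open.

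**A reader might also infer that segmented regression should give way to a dyad-level before/after comparison.** With 180 spread evenly and independent observations, the level change detectable with 80% power is about 1.57 SD for carer burden (3.3 a month) and 1.11 SD for quality of life (6.7 a month). A two-sample comparison detects 0.74 SD (30 v 30) and 0.52 SD (60 v 60). But the same 18 monthly means without trend terms already detect 0.77 and 0.54 SD, so almost all of the gain comes from dropping the trend terms. In a study without a control group, adjustment for prior trend is the protection that the Discussion claims. Giving it up is a trade-off that the arithmetic mismatch does not justify.

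**The primary analysis does not use the 180.** It rests on up to 300 checklists a month. This stands and lowers the severity.

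**Conclusion.** The concern holds in this form: the selection rule and the total of 180 cannot both describe the same 18 months unless about one third of clinician-months yield a dyad, or interviews run for only part of the study. The article says neither. The discrepancy is 540 against 180 at most.

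The consequence is conditional. If 180 is a cap filled in sequence, post-intervention dyads number 0 at a yield of two thirds or more, 45 at 50% and 90 at one third. This assumes 30 clinicians retained throughout and a yield constant over time.

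The point should be corrected, but it is not critical. It bears on the secondary aim and on the verification of self-reported adherence, not on the primary analysis itself.

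**What to change.** Reconcile the two figures in Participants and in the Abstract, in one of two ways.

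1. **Keep 180.** Change the rule to one assenting dyad per clinician every third month, staggered in three groups so that about 10 clinicians contribute each month, with each collaborative spread over the groups. That is 18 / 3 = 6 dyads per clinician, 3 before and 3 after the intervention, and 30 x 6 = 180 in all (about 90 and 90). It needs no interviews beyond those already planned. Incomplete yield would bring the number below 180, which fits the Abstract's wording of a maximum. The cost is fewer dyads per month than under the monthly rule.
2. **Keep the monthly rule.** State the total as up to 540, with the expected yield. The cost is up to 540 - 180 = 360 more dyads, each with two interviews, so up to 720 more calls.

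Under either option, state how the dyads are distributed over the 9 pre-intervention and 9 post-intervention months, and keep trend adjustment in the analysis of client outcomes.
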